### Data collection and management

Evaluation of this implementation-effectiveness project will require data collection from two main sources: (1) primary data collected from participants and (2) secondary de-identified data collected from external providers, including MHA’s electronic records, state-based data custodians (eg, NSW Centre for Health Record Linkage) and the panel survey company. Secondary data will be stored and analysed in accordance with the requirements of external data providers.

#### Participant-level data

All participant-reported data collection will be conducted externally to MHA by the research team. Data collected from participants will include baseline demographic data (eg, age, sex, education level) from both the preupgrade and postupgrade cohorts, as well as the individuals participating in qualitative interviews or focus groups. For a full list of participant collected data and timepoints, see online supplemental appendix A.

Cohort questionnaires will be administered at baseline (within 10 days of initial helpline service utilisation), 3 and 6 months postinitial service utilisation. All participant collected data will be automatically assigned a unique study identification code and stored and managed using REDCap electronic data capture tools hosted at the University of Sydney.^35 57^ Qualitative data collected during interviews, including transcripts of interviews, will be stored in a password-protected folder in the highly protected SharePoint folder hosted by the University of Sydney. Only designated research team members will have access to this data.

#### Secondary data

ED population-level data: Deidentified, aggregated data on monthly ED presentations for LBP among patients aged ≥18 years will be obtained from the Mid North Coast Local Health District. Presentations will be identified using the International Classification of Diseases 9th and 10th editions and Systematized Nomenclature of Medicine-Clinical Terminology (SNOMED CT) diagnostic codes adapted from Anderson *et al*^58^ (see online supplemental appendix B). Data will be extracted through the Emergency Department Data Collection via the NSW Centre for Health Record Linkage. Extraction will cover the 18 months before and after the helpline upgrade. Panel data: Deidentified and aggregated population awareness of the helpline will be collected via panel surveys. These will be administered by a panellist provider premedia and postmedia campaign and stored on the University of Sydney’s highly secure SharePoint site. MHA data: Deidentified demographic data routinely collected by MHA, including aggregated information on age, sex, physical activity, pain severity and area of residence, will be compared with demographic data of the cohorts to assess for selection bias.

### Data analysis

Quantitative data will be analysed to evaluate the reach, effectiveness, adoption and implementation dimensions of the RE-AIM framework. Descriptive statistics will summarise demographics and key characteristics of helpline callers, cohort participants, campaign survey respondents and individuals presenting to the Mid North Coast Local Health District ED with LBP. Descriptive statistics will also be used to summarise the fidelity of the delivered helpline service, with the proportion of total calls rated as poor, average, good or high. Participant-reported acceptability will be summarised visually using stacked horizontal bar charts to display the proportion of respondents selecting each response category across the seven acceptability domains.

A χ² test will be used to compare the postcampaign proportion of individuals aware of the helpline between the control region and the intervention region (exposed to the media campaign). Data collected prior to the campaign will be used to provide a descriptive comparison of baseline awareness between the two regions. If notable baseline differences in awareness are identified, a logistic regression will be conducted to estimate the association between the region (intervention or control) and postcampaign awareness, adjusting for baseline awareness as a covariate. An interrupted time series with segmented regression and a generalised Poisson or negative binomial model (dependent on data overdispersion) will be used to evaluate the impact of the media campaign (eg, the interruption point)^59^ on the monthly helpline call rate, the monthly helpline call rate stratified by age, sex and rurality demographics, and the monthly rate of ED presentations for LBP within the campaign exposed Local Health District. Exploratory analyses will be conducted to inspect visual trends, with adjustments for autocorrelation and seasonality conducted prior to final analysis. The estimated impact of the media campaign on each outcome, for example, an immediate (stepped change) or trend change (slope change) will be prespecified in the statistical analysis plan once the final media strategy has been determined.

A comparison of primary participant-reported outcome (self-reported healthcare service utilisation) and secondary outcomes, between the preupgraded and postupgraded helpline cohorts will be conducted. The primary outcome will be analysed at 3 months (as part of the effectiveness dimension) and 6 months (as part of the maintenance dimension). Healthcare service use will be collected as count data and analysed using negative binomial regression model. The rate ratio will be estimated comparing the postupgrade cohort to preupgrade cohort. Negative binomial regression will account for individual follow-up time and potential overdispersion due to non-independence of repeated measures. Matching with replacement will be used to address potential imbalances between cohorts in baseline demographics and to account for the anticipated smaller ‘unexposed’ preupgrade cohort compared with the larger ‘exposed’ postupgrade cohort. Sensitivity analyses will be conducted to assess the robustness of the findings.

Individual qualitative interviews will be conducted with purposively selected cohort participants to identify factors and processes that contributed to the helpline uptake, implementation and future scalability. These include acceptability and appropriateness (the extent to which the helpline is perceived as agreeable and relevant); advertising campaign effectiveness; individual factors (eg, participants’ socioeconomic status); and service outcomes (eg, the extent to which the helpline is perceived to be effective, patient centred, timely). Interviews will be semistructured, using a mixture of inductive and deductive thematic analysis drawing on the PRISM framework.^36^ An interview guide will be used to ensure the same topics are explored across individual interviews.

Focus groups with key stakeholder groups will be conducted online to identify factors and processes that contributed to helpline uptake, implementation and future scalability. The interview guide will be informed by findings from the implementation phase to align with observed barriers and enablers. Focus group data will be analysed using a combination of inductive and deductive approaches, drawing on the PRISM framework to guide interpretation.

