#### Campaign awareness survey

Media campaign awareness will be assessed using a separate online panel survey administered by a commercial panel provider, with data that can be weighted to the regional population. The company will purposively recruit a sample of adults (≥18 years) residing in the Mid North Coast and residing in a comparison area, the Southern NSW Local Health District. A single campaign awareness question will be asked within existing panel surveys. This will allow us to determine campaign awareness in the exposed region and in a demographically similar region. Only aggregated, deidentified responses will be provided to the research team; therefore, individual informed consent is not required in accordance with institutional ethics approval.

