### Evaluation

The RE-AIM framework^37^ will be used to evaluate the implementation and effectiveness of the upgraded helpline service. The framework includes five dimensions (RE-AIM) used to understand and evaluate the broader impact of the implementation and intervention across individual, setting and system levels (see table 1). PRISM^36^ will be used as an extension of the RE-AIM framework to guide the exploration of the contextual factors that influence the project outcomes. This includes the characteristics and perspectives of recipients (eg, helpline operators, stakeholders and users), the implementation and sustainability infrastructure (eg, helpline operator capacity vs caller demand), and external environment related to long-term sustainability and scalability of the helpline (eg, government funding and policies for primary care). It can also be used to understand and guide necessary adaptations to improve the intervention implementation process.^49^

**Table 1 T1:** Evaluation of implementation and effectiveness using the RE-AIM framework

Evaluation outcome	Study design	Data source	Time points	Outcome measure	Data analysis	Sample size
Reach						
Reach of the media campaign Reach of the helpline	Cross- sectional Interrupted time series	Population panel surveys Monthly helpline call numbers	(1) Pre–post media campaign (2) 18 months pre to 12 months postmedia campaign	Comparison of helpline awareness between two Local Health Districts LBP monthly call rates	χ² test for proportions Segmented regression	700 panel survey participants (post campaign) All LBP phone calls/services received
Effectiveness						
ED visits for LBP (population level) Self-reported healthcare service utilisation (individual level)	Interrupted time series Independent pre–post cohort design	All LBP ED visits recorded in the Local Health District targeted by the media campaign Pre/Post helpline cohort self-reported data.	18 months pre–post upgrade Baseline, 3 months for each cohort	Monthly LBP ED visits Self-reported healthcare service utilisation	Segmented regression Negative binomial regression for count of healthcare service utilisation	All adult ED LBP visits registered with corresponding health district database 295 cohort participants
Adoption						

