#### Reach

Reach will be assessed to determine the extent to which the media campaign raises awareness of the helpline and influences service utilisation. This will be evaluated using two approaches:

(1) To evaluate media campaign reach, we will conduct population-based surveys in the ‘intervention’ region (the Mid North Coast Local Health District of NSW) targeted by the campaign, and a ‘control’ region (Southern NSW Local Health District) that will remain unexposed to the media campaign. The control region was chosen for its similarity in population size and distribution to the intervention region, as well as the geographical distance of approximately 450 km and different media markets, which are expected to minimise campaign crossover. Surveys will be administered online via a commercial panel company. The survey will include a single campaign awareness question assessing recognition of the helpline service along with basic aggregated demographic information (eg, age group, sex and postcode) to enable region comparisons. Surveys will be conducted at baseline (precampaign) and postcampaign to measure population awareness of the helpline. Sample size calculations are based on the postcampaign comparison between the two regions (baseline awareness will be summarised descriptively). Based on feasible sample sizes provided by the panel company, a total of 300 respondents in the intervention region and 400 in the control region will be surveyed at both time points. Assuming 0.05% of respondents are aware of the helpline in the control group, this provides 85% power to detect a 3% difference in awareness between regions at a two-sided significance level of 5%.

(2) To evaluate the impact of the campaign on service use, we will analyse the monthly call rates using retrospective data to compare the rates of unscheduled calls with a primary complaint of LBP. This will be analysed 18 months before and 12 months after the campaign begins. An interrupted time series design will be used to determine the effect of the media campaign on call volume.

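### The fallback logistic regression for campaign awareness adjusts for a baseline value that exists only per region, so the adjusted region effect cannot be estimated and any pre-existing regional gap stays uncorrected

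*Protocol article*

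**What the plan says.** All references are to the protocol article.

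- **Main awareness analysis** (Data analysis): "A χ² test will be used to compare the postcampaign proportion of individuals aware of the helpline between the control region and the intervention region". Precampaign data are used descriptively.
- **Fallback** (Data analysis): "If notable baseline differences in awareness are identified, a logistic regression will be conducted". It is to estimate the "association between the region (intervention or control) and postcampaign awareness, adjusting for baseline awareness as a covariate".
- **Design** (Evaluation, Table 1): media campaign reach is listed as cross-sectional. The interrupted time series in the same cell belongs to the helpline call numbers.
- **How the item is asked** (Campaign awareness survey): "A single campaign awareness question will be asked within existing panel surveys".
- **What the team receives** (Campaign awareness survey): "Only aggregated, deidentified responses will be provided to the research team". The Secondary data section repeats this: "Deidentified and aggregated population awareness of the helpline will be collected via panel surveys".
- **Size** (Reach): "a total of 300 respondents in the intervention region and 400 in the control region will be surveyed at both time points". With 0.05% awareness assumed in the control region, this is said to give 85% power for a 3% difference at a two-sided 5% level.

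No section describes re-contacting the same respondents, linking the waves, or a model that uses both waves together.

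**The concern.** Adjusting a respondent-level outcome for baseline awareness needs a baseline value that varies within region. The survey as described supplies one proportion for the intervention region and one for the control region. With two regions, that covariate carries the same information as the region indicator, and the two effects cannot be separated.

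The regions were not randomised, and this model is the only planned adjustment for a pre-existing difference in awareness. Such a difference is possible, because the helpline has operated nationally since 2011 (Introduction). If the model cannot be fitted, the formal comparison left is the postcampaign one, which credits any earlier gap to the campaign.

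**Working it through.** **1. The plan's own power figure.** Inputs from Reach: 300 intervention, 400 control, control awareness 0.0005, difference 0.03 (read as 3 percentage points), two-sided 5%.

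- SE = √(0.0305 × 0.9695/300 + 0.0005 × 0.9995/400) = 0.00999
- Power = Φ(0.03/0.00999 − 1.96) = 0.851

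The stated 85% is reproduced with the unpooled normal approximation. Enumerating the uncorrected chi-square test gives 98%. The size of the survey is not in question.

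**2. Can the fallback be estimated?** Let R = 1 for the intervention region and 0 for control, with regional baseline proportions b₁ and b₀. The covariate for any postcampaign respondent is

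B = b₀ + (b₁ − b₀)R.

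Put this into the planned model:

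logit(p) = α + βR + γB = (α + γb₀) + [β + γ(b₁ − b₀)]R.

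Only the two bracketed quantities can be estimated, so β and γ cannot be separated. A numerical check with 700 respondents agrees: the matrix (intercept, region, regional baseline) has rank 2 for 3 columns, and region and baseline correlate at 1.00. With γ dropped, what remains is the unadjusted region contrast.

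**3. What stays uncorrected.** An illustration with assumed rates: baseline 2% v 0.5%, postcampaign 5% v 0.5%.

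- Postcampaign difference: 5 − 0.5 = 4.5 points
- Net change: (5 − 2) − (0.5 − 0.5) = 3.0 points
- Baseline gap credited to the campaign: 1.5 points

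**4. Error when the campaign does nothing.** Postcampaign rates equal baseline rates. The figures are the exact probability that the uncorrected chi-square test (300 v 400) finds significantly higher awareness in the intervention region; the nominal value in that direction is 2.5%.

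| Baseline, intervention v control | Probability |
|---|---|
| 2% v 1% (assumed) | about 20% |
| 3% v 1% (assumed) | about 49% |
| 0.05% v 0.05% (plan's rate in both regions) | negligible |

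For the last row, with no aware control respondent the statistic for x aware of 300 is 700 × 400x/[300(700 − x)]. This is 2.67 at x = 2 and 4.02 at x = 3, so at least 3 are needed. With 300 × 0.0005 = 0.15 expected, the chance of that is about 0.15³/6 × e^(−0.15) ≈ 0.0005.

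**5. Can a replacement be estimated from the same data?** A two-wave model with region, wave and region × wave has rank 4 of 4 and needs only the four region-by-wave counts. Power for a 3-point gain:

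| Baseline in both regions | Postcampaign chi-square (enumerated) | Difference-in-differences (Wald, simulated) |
|---|---|---|
| 0.05% (plan's rate) | about 98% | about 94% |
| 1% (assumed) | about 76% | about 55% |

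**The case against.** **Linked respondents.** The wording that both samples are surveyed at both time points could mean the same people are asked twice. Table 1 says cross-sectional, and aggregated delivery would still withhold an individual baseline value. This reading does not rescue the model.

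**Stratum-level baselines.** Reach says that aggregated age group, sex and postcode accompany the awareness item. A baseline proportion per stratum within region would not be exactly collinear with region (rank 3 of 3 in a test). That is correct algebraically, but the article does not describe such a model. At 0.05% awareness only 400 × 0.0005 = 0.2 aware control respondents are expected, so nearly all stratum values would be zero.

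**Importance.** The fallback is conditional and serves one of two reach measures. Baseline awareness will be reported for both regions, so a gap would be visible though uncorrected. This stands, and it limits the severity.

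Three stronger readings might be inferred and are not supported:

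- *That the awareness evaluation has no working analysis.* The chi-square test can be carried out and is the comparison on which the sample size rests.
- *That the missing threshold for a notable baseline difference is itself a fault.* The article refers to a statistical analysis plan that is not shown, and a threshold belongs there.
- *That an infinite odds ratio defeats the model.* At 0.05%, zero aware of 400 has probability 0.9995^400 = 82%. This is a sparse-data matter that exact or penalised methods can handle, and it is separate from collinearity. It also does not combine with the examples that assume 1% in control, where that probability is 0.99^400, about 2%.

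**Conclusion.** The fallback model cannot deliver a baseline-adjusted region effect from the data the article describes. This follows from the stated design and does not depend on any assumed rate. It rests on one premise: that baseline awareness enters as a single proportion per region, the only form the article supports.

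The practical size does depend on assumptions, because the article gives no observed baselines. It ranges from negligible at the plan's 0.05% in both regions to a false finding in favour of the campaign in about 20% (2% v 1%) or 49% (3% v 1%) of cases. A reader might take this as undermining the trial's main results, but it does not. It affects a conditional analysis of media campaign reach and leaves the powered chi-square test, the call-rate time series and the primary healthcare-use outcome untouched. Severity: should be fixed, ideally before postcampaign data arrive, since a replacement chosen afterwards would be post hoc.

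**What to change.** Replace the logistic regression sentence in Data analysis with a two-wave analysis of the four region-by-wave counts:

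- Define the baseline-adjusted campaign effect as (post − pre, Mid North Coast) − (post − pre, Southern NSW), on the risk-difference scale, with an interval suited to sparse cells.
- Report it beside the postcampaign chi-square test. Where baselines differ, base the conclusion about the campaign on this contrast.
- State its power, because the sample size was set for the postcampaign comparison only.

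Alternatively, if a linked panel is intended, say so and arrange for linked respondent-level data. That would also change the statements on aggregated delivery and on consent.

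The first option costs wording only, since both survey waves are already planned. Its price is precision when awareness is not near zero: about 21 points of power at an assumed 1% baseline in both regions (76% − 55%), but only about 4 at the plan's 0.05% (98% − 94%). Keeping the chi-square test as the comparison on which the sample size rests preserves the existing justification.

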### Testing and refinement

The upgraded helpline service and workflows will be tested through a two-step process: (1) A pilot phase with a small number of invited pilot users (non-public release). Pilot users will include members of our research partner organisations, project operations team and MHA’s consumer advisory group, ensuring representation from each partner. We anticipate a minimum of five users. Pilot users will complete the System Usability Scale^40^ to provide structured feedback on the usability of the helpline service. This process will be complemented by an online consultation with pilot users to explore the service functionality, ease of navigation and helpline operator communication. (2) Initial implementation trial and refinement 6 months prior to the media campaign. This will allow time to test the upgraded service in ‘real-world conditions’ prior to the media campaign and an anticipated increase in service users. It is estimated this will involve 50 participants based on MHA’s current monthly rate of LBP callers. These participants will be recruited consecutively following use of the helpline service (see the participant consent and recruitment section) and form the first 50 participants of the postupgrade cohort.

Cohort participants will rate their acceptability of the helpline service across several domains using a modified version of the Theoretical Framework of Acceptability Questionnaire (TFAQ).^41^ In addition, routine service information including the number of calls, call answer rates, peak call times, call duration, number of urgently referred cases, proportion of calls requiring follow-up and average follow-up calls will be collected in the initial implementation period (prior to the media campaign release).

This information will be combined to identify any operational, logistic or technical adaptations that need to be made prior to the full implementation stage.

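### The interrupted time series breaks only at the media campaign although the upgraded helpline goes live 6 months earlier, so the campaign effect cannot be separated from any upgrade effect, and the windows and anchors disagree

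*Protocol article*

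**What the plan says.** All places are in the protocol article.

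- **Interruption.** Data analysis: segmented regression "will be used to evaluate the impact of the media campaign (eg, the interruption point". This covers the monthly call rate, the call rate by age, sex and rurality, and ED presentations in the campaign district. The Reach and Effectiveness sections also tie the series to the campaign. Data analysis leaves the shape of the campaign effect, step or slope, to the statistical analysis plan.
- **Upgrade date.** Testing and refinement: "Initial implementation trial and refinement 6 months prior to the media campaign", and "This will allow time to test the upgraded service in ‘real-world conditions’ prior to the media campaign". The upgraded service is thus in public use during the lead-in.
- **Window for calls, Reach.** "This will be analysed 18 months before and 12 months after the campaign begins"; Table 1 agrees ("18 months pre to 12 months postmedia campaign").
- **Window for calls, Adoption.** The Adoption row of Table 1 uses the same monthly calls, stratified, but takes 18 months on each side of the helpline upgrade.
- **Window for ED.** Table 1 has "18 months pre–post upgrade", and Secondary data has "Extraction will cover the 18 months before and after the helpline upgrade".

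Nothing in the article mentions a term for the upgrade, a phase-in period, or exclusion of the lead-in months.

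**The concern.** Two events occur 6 months apart and the model recognises one. If the upgrade itself changes unscheduled low back pain calls or ED visits, that change sits at the end of the precampaign segment. A single-interruption model reads it partly as precampaign trend and projects it forward as what would have happened without the campaign.

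The ED series has a further problem. It is collected around the upgrade, labelled as an effectiveness outcome of the helpline, and interrupted at the campaign. A reader cannot tell which event the result is meant to evaluate.

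The distinction matters to the project's own aims. Campaign costs enter the cost-effectiveness analysis, and scale-up through a broader campaign is to be judged from this evaluation (Maintenance section).

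**Working it through.** The article gives no power, effect size or precision figure for the time series, so there is no stated figure to reproduce.

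**1. Windows on one axis** (campaign = month 0, upgrade = month -6)

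| Series | Stated window | On the campaign axis | Precampaign months, old + upgraded |
|---|---|---|---|
| Calls, Reach | campaign -18/+12 | -18/+12 | 12 + 6 (one third upgraded) |
| Calls, Adoption | upgrade -18/+18 | -24/+12 | 18 + 6 (one quarter upgraded) |
| ED | upgrade -18/+18 | -24/+12 | 18 + 6 (one quarter upgraded) |

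The end points coincide. The start points for the same calls differ by 6 months.

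**2. Spurious campaign effect.** Assume a log-rate step d at the upgrade, no campaign effect, and a least-squares model with intercept, trend, campaign step and campaign slope. With n precampaign months, Sxx = n(n² - 1)/12.

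- n = 18: Sxx = 18 × 323/12 = 484.5. The 6 upgraded months lie on average 6 months after the segment's centre. Precampaign slope = 6 × 6d/484.5 = 0.074d per month, and the fitted slope change is -0.074d. The segment mean is 6d/18 = 0.333d and the postcampaign centre is 15 months later. Mean effect = d - (0.333 + 15 × 0.0743)d = **-0.45d**. Month 12 is 20.5 months from the centre: d - (0.333 + 20.5 × 0.0743)d = **-0.86d**.
- n = 24: Sxx = 24 × 575/12 = 1150. Slope = 6 × 9d/1150 = 0.047d. Mean effect = d - (0.25 + 18 × 0.047)d = **-0.095d**. In the first month it is d - (0.25 + 12.5 × 0.047)d = +0.16d, so the initial step and the slope largely cancel.

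As an illustration, noise-free Poisson fits with 18/12 months and a true campaign rate ratio of 1.00 give these month-12 ratios. The upgrade effects are assumptions.

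| Assumed upgrade effect | Apparent campaign rate ratio, month 12 |
|---|---|
| none | 1.00 |
| step 0.9 | 1.09 |
| step 1.1 | 0.92 |
| step 1.2 | 0.85 |
| step 1.5 | 0.68 |
| slope +5% per month | 1.74 |

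An upgrade step term restores 1.00 in every step scenario. The slope scenario also needs an upgrade slope.

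**3. Why the ED anchor matters.** Suppose the break is put at the upgrade (18/18) and a true step c occurs at the campaign, 6 months later. With a common trend and one step, the pooled slope is 12 × 3c/(2 × 484.5) = 0.0372c. The estimated step is 12c/18 - 18 × 0.0372c, about zero. A campaign rate ratio of 0.90 would then be reported as a step of about 1.00; with the break at the campaign it is recovered as 0.90.

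**4. Precision.** Standard error of the mean 12-month campaign effect in residual SD, with independent errors and no seasonal terms. The variance is 1/12 + 1/m + g²/S, where m is the number of months in the reference segment, g the distance from its centre to the postcampaign centre, and S the sum of squares that informs the slope.

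| Model | 18/12 | 24/12 |
|---|---|---|
| Campaign only | √(1/12 + 1/18 + 15²/484.5) = 0.78 | √(1/12 + 1/24 + 18²/1150) = 0.638 |
| + upgrade step | √(1/12 + 1/6 + 9²/160.5) = 0.87 | √(1/12 + 1/6 + 9²/502) = 0.641 |
| + upgrade step and slope | √(1/12 + 1/6 + 9²/17.5) = 2.2 | 2.2 |
| Lead-in months excluded | √(1/12 + 1/12 + 18²/143) = 1.6 | √(1/12 + 1/18 + 21²/484.5) = 1.0 |

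Here 160.5 = 143 + 17.5 and 502 = 484.5 + 17.5. The third model stays at 2.2 for any pre-window, because only the 6 lead-in months inform the projected slope.

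**The case against.** The strongest reply is that no bias has been shown. A reader might infer from the design that the campaign estimate is biased. The documents do not support that. They give no upgrade effect, and they forecast the lead-in at the existing volume: "It is estimated this will involve 50 participants based on MHA’s current monthly rate of LBP callers". The rise in users is expected with the campaign. The call outcome counts unscheduled calls, so the new follow-up calls need not inflate it. About 50 lead-in users of a national service are unlikely to move ED counts in a district of 230 000. All of this stands.

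A reader might also compute that 67% (18/12) or 75% (24/12) of an upgrade step would be credited to the campaign. Those figures come from a model without a trend, which is not the segmented regression described.

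It can further be said that model terms belong in the statistical analysis plan. That stands only in part. The article defers the shape of the campaign effect, whereas it names the interruption itself, and the conflicting windows are in the published text.

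Finally, the participant-level primary outcome is a separate cohort comparison and is untouched, and the windows share an end point. Both are correct and limit the severity.

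**Conclusion.** The point holds as a problem of separation and consistency. With one interruption at the campaign and the upgrade live 6 months earlier, the plan cannot distinguish a campaign effect from any upgrade effect. The resulting bias is zero if the upgrade leaves the series unchanged. Otherwise its size and sign depend on the unknown d and on the model form: on average -0.45d for Reach (18/12) and about -0.10d for a 24/12 series, under a step-plus-slope model with a pure upgrade step.

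For ED, a material bias from the lead-in is unlikely, and the stronger point is the contradictory anchor. For calls, the risk is real but of unknown size, and the two windows for one series need reconciling.

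Severity: should fix. The conclusion assumes that the 6-month lead in the text is the actual interval; the timeline figure was not available for checking.

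**What to change.** 1. In each series, add an upgrade step at month -6 and report it separately from the campaign effect.
2. Keep an upgrade slope, and exclusion of the 6 lead-in months, as sensitivity analyses only. As main analyses they would raise the standard error to about 2.2 (either window) and to 1.0 (24/12) or 1.6 (18/12) residual SD.
3. State for each series which event it evaluates: upgrade, campaign, or both.
4. Use one common window, for example campaign -24/+12, and make Table 1 and the Reach, Effectiveness, Secondary data and Data analysis sections agree.

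The cost is mainly wording. The ED and Adoption windows already span campaign -24/+12, so no additional data are needed. The upgrade step raises the standard error from 0.78 to 0.87 residual SD if 18/12 is kept, and from 0.638 to 0.641 with 24/12. A longer pre-window is optional: with 36 precampaign months the upgrade-step model would give √(1/12 + 1/6 + 9²/2265) = 0.53, but it would not rescue a model with a separate upgrade slope.
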